### Data collection

All the study sites will perform a baseline assessment with the instruments selected in the preparation phase and a biannual/annual assessment of the outcomes.^1^.

### Outcomes

Each site in the study will assess at least one of the following outcomes:

Incidence of frailty^2^ (e.g. surrogate markers including ADL/IADL impairment and/or reducing socio-economic resources and/or risk of adverse healthcare outcomes such hospitalization, institutionalization, death)Progression/regression of risk of negative outcomesIncidence of hospitalizationIncidence of institutionalizationIncidence of death

Each study site may add different outcomes listed in the specific study site section

### Sample

Subjects for inclusion/assessment will be aged over 64 years and living at home; those living in an institution (nursing homes or similar) will be excluded. Each study site can decide to restrict the field of intervention with additional exclusion criteria. The total number of European citizens involved in the assessment will be around 2000 for each outcome of which at least 20% will be enrolled before the end of June 2016.

Participants will be enrolled among the ones who access the services managed by the stakeholders involved in the proposal. In Ireland, participation in the study will be offered to community-dwelling older adults who are under surveillance by their Public Health Nurse consistent with ongoing studies in this setting [10, 13, 14]; in Valencia participant will be the women who access the outpatients department of the University Hospital gynecologic service for health control. In Genoa participants to the DOREMI project will be enrolled enrolled involving citizens who access to the local University Hospital. In Barcelona participants will be enrolled among communitydwelling older adults who are attended by their primary health care team, both in the office and at home. In Twente and Campania, community dwelling older adults will be enrolled among participants to the PERSSILAA project, patients referring to Federico II outpatients practices and to the GPs of the Salute in Collina no profit organization. Campania study sample will also include participant to the Sunfrail pilot, and to the Beyond Silos project in Salerno. In Rome the over-74 citizens reached by the Viva gli Anziani program (all living in the community) will be included in the study. In Porto participants will be primary care patients of Health Centers that agreed to participate. People over 64 years will be prescreened by trained GPs and further assessed by the CARTS project team, supported by the General Directorate of Health. In Parma the over 64 citizens of Central District of Parma will be included as part of Sunfrail and SprinTT recruitment process. In Pecs community dwelling older adults will be enrolled from members and clients of local NGO’s Wherever possible the General Practitioner of the citizens involved in the study will be informed.

### Sample size

– Alpha error = 5%– Power = 80%– Confidence Level = 95%– Confidence Interval = 1%– Population = 28,737,910^3^– Expected reduction of frailty incidence = 2.5%– Expected reduction of hospitalization rate = 5%– Expected reduction of Institutionalization rate = 5%– Expected reduction of death rate = 2.5%– Test 1 Proportion (observational study) superiority: sample size needed per single outcome = 2,000 subjects (including 10% of lost-to-follow up)^4^– Comparisons will be carried by applying the observed/expected approach on the basis of data stemming from the existing data flows available in the different study sites (national, regional or local data flow). The stratification of risk carried out by administering the baseline assessment will allow also transnational comparisons

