* Total budget, in brackets: the budget obtained from the EU

**Table 3 t3-tm-15-53:** summary of the study design according to the implementation sites

Study site	Population^5^	Study design	Tools	Activities	Outcomes	Source(s) of comparison
Barcelona	Over 64 (1000 ind.s)	Prospective observational	-SFGE - RISC	-Frailty Pro-active screening/stratification and monitoring of community dwellers. -Referral to formal community-based or hospital-based services in case of need. - Community-based social activities including health promotion - Psychoeducational programmes for informal caregivers -Introduction of harmonised care bundles addressing multimorbidity, cognitive function and nutrition	Incidence of hospitalization Incidence of institutionalization Incidence of death	Official sources Data from different representative elderly cohorts in Catalonia, CARTS project in Cork, Porto and Galway. data stemming from the same sample according to a before-after interrupted-time series design
Cork	Over 64 (5000 ind.s)	- Prospective observational - Randomised trial (pilot)	-CFS -CARTS -RISC -SFGE	-Frailty screening/stratification -Targeted intervention	Incidence of frailty Progression of frailty Incidence of hospitalization Incidence of institutionalization Incidence of death	CARTS project in Galway
Galway	Over 64 1000 ind.s	Prospective observational	-CFS -CARTS -RISC -SFGE	-Pro-active frailty screening/stratification and monitoring -Introduction of a harmonised care bundle, common to the community-hospital interface (i.e. an integrated care pathway). -Referral to formal community-based or hospital-based services in case of need.	Progression of frailty Incidence of hospitalization Incidence of institutionalization Incidence of death	The CARTS project in Cork as a sister study. Retrospective data on older adults attending University Hospital Galway during the corresponding period one year before the interrupted time series study commences.

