Parma	Over 64 (1000 ind.s)	Prospective observational	-Sunfrail -SFGE -RISC	-Pro-active frailty screening of 1000 over-65 citizens followed by comprehensive geriatric assessments -Referral to day services or day-hospital-based services in case of need -Strengthening the social network around the frails -Activation of nutritional, physical exercise and technological monitoring interventions with specific targets: -Prevention of falls -Prevention of negative consequences of social isolation -Prevention of Malnutrition	Incidence of frailty Progression of frailty Incidence of hospitalization Incidence of institutionalization Incidence of death	Official sources (report on the hospitalization and mortality in Emilia Romagna region released annually by ISTAT and Ministry of Health);
Pecs	Over 64 (200 ind.s)	Prospective observational	-SFGE -RISC	-Frailty screening -training of the target group) on ICT skills -training of informal caregiver network on the use novel assessment and training tools. -widespan public awareness raising campaign of the general public in all participating countries	Incidence of hospitalization Incidence of institutionalization Incidence of death	official statistical data of the National Health Insurance and Statistical Bureau
Oporto	Over 64 (300 Ind.s)	Prospective double arm observational	- RISC	-A training program for PC professionals on frailty and dementia screening and intervention -A awareness program for the general community on frailty and dementia issues. -A psycho-educational program for caregivers of old people frail or with dementia. -A cognitive stimulation program for people with cognitive frailty or MCI	Incidence of hospitalization Incidence of institutionalization Incidence of death	Control group
Rome	Over 74 (4500 ind.s)	Prospective observational	-SFGE -RISC	-Pro-active frailty screening/monitoring -Home visits -Assistance in bureaucratic tasks -Referral to formal community-based or hospital-based services in case of need -Strengthening the social network around the frails -Community-based social activities including health promotion with specific targets	Incidence of hospitalization Incidence of institutionalization Incidence of death	Official sources (report on the hospitalization and mortality in Campania region released annually by ISTAT and Ministry of Health); data stems from the ongoing Lazio Region Frailty Study carried out by the University of Tor Vergata,

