**S 2**	Set up of a methodology to find out the impact of the public health program in this field It will be based on the agreement about the use of one methodology to assess frailty at baseline 12 and 24 months of observation (main candidate the RISC questionnaire – CARTS program), and to identifying common outcomes to be evaluated after 12/24 months of observation. Data will be gathered into one database that will be the main source of the evaluation. Comparative data will stem from official data source (mortality data, institutionalization rate, hospitalization rate, cost of services) which encompass the studied population. Specific observational cohorts could be included in local trials aimed to assess the impact of the interventions: this kind of approach could take longer than the first three months to be set up. Additional tools to assess specific aspects of the projects supporting the proposal, which are already used, could be included to improve the assessment methodology.	15-Jan-2016	31-Mar-2016	Six Countries	
**S 3**	Risk Classification of the first 20% of the sample About 200–400 citizens	1-Apr-2016	30-Jun-2016	Six countries	Report on the baseline assessment
**S 4**	First six months Impact assessment	1-Nov-2016	31-Dec-2016	Six countries	Report on the impact assessment on the citizens assessed before the 30 June 2016

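### The 2,000 per outcome cannot be the 80%-power superiority size for all four stated reductions on any one scale at credible rates, and the planned totals do not agree

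*Protocol article*

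**What the plan says.** The Sample size section lists alpha 5% and power 80%. Beside them it lists precision inputs: "Confidence Level = 95" (per cent), an interval of 1%, and a population of 28,737,910. It expects a 2.5% reduction for frailty incidence and for death ("Expected reduction of death rate = 2.5", per cent) and a 5% reduction for institutionalization and for hospitalization ("Expected reduction of hospitalization rate = 5", per cent). From these it draws one size for every outcome: "Test 1 Proportion (observational study) superiority: sample size needed per single outcome = 2,000 subjects (including 10% of lost-to-follow up". The comparison is to be observed against expected, using existing data flows.

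The planned number appears in four other places:
- The Abstract gives 2,000 per outcome as a minimum.
- The Sample section says "The total number of European citizens involved in the assessment will be around 2000 for each outcome".
- Table 4, sprint S3, says "Risk Classification of the first 20% of the sample About 200–400 citizens".
- Table 3 lists site numbers that include "Over 64 (5000 ind.s" for Cork and "Over 74 (4500 ind.s" for Rome.

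**The concern.** A one-proportion superiority test needs a reference rate, an alternative rate, alpha, sidedness and power. It uses neither an interval width nor a population size. The section prints the two inputs that the test does not use and, in the visible text, omits the reference rate, the scale of the reduction and the sidedness.

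Halving the effect multiplies the required number by about four at a similar rate. One figure therefore cannot be the 80% size for both a 2.5% and a 5% reduction unless the reference rates happen to differ in just the right way.

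The stated 80% is what readers will use to interpret a null result. If the reductions are relative and about 2,000 people are analysed, a null result is likely even if the programmes work as expected. It could then be read as evidence of no impact.

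**Working it through.** **Inputs.** From Sample size: alpha 5%, power 80%, 10% loss, reductions of 2.5% and 5%, interval 1%, confidence level 95%. Evaluable number: 2,000 × 0.9 = 1,800. The reference rates below are assumptions, because the visible text gives none.

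**1. Trying to reproduce 2,000.** The labelled test cannot be run without a reference rate. A precision calculation with the printed 1% as half-width and an assumed proportion of 5% gives

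1.96² × 0.05 × 0.95 / 0.01² = 1,825

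The finite-population correction for 28,737,910 does not change this. Adding 10% gives 2,007; dividing by 0.9 gives 2,028. Both are close to 2,000. With proportions of 2.5% and 10%, the same formula gives 937 and 3,458 before allowing for loss.

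**2. The superiority test.** With reference rate p0 and reduced rate p1,

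n = [z_α √(p0(1−p0)) + 0.842 √(p1(1−p1))]² / (p0−p1)²

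where z_α is 1.960 two-sided or 1.645 one-sided.

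*Absolute, 5 points.* Two-sided n is 238 at a 10% rate and 783 at 50%. The maximum over all rates is about 783, or about 870 enrolled. Power with 1,800 is about 99% or more at every rate.

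*Absolute, 2.5 points.* At p0 = 18% and p1 = 15.5%: (0.7530 + 0.3046)² / 0.025² = 1,790, and 1,790 / 0.9 = 1,989.

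| Reference rate | Evaluable n, two-sided | Power with 1,800 |
|---|---|---|
| 10% | 1,049 | 96% |
| 18% | 1,790 | 80% |
| 20% | 1,949 | 77% |
| 30% | 2,597 | 64% |
| 50% | 3,137 | 56% |

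Power stays below 80% until the rate reaches about 83%, then recovers. One-sided, the lower crossing is near 25%.

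*Relative.* For a 5% reduction at p0 = 20%, p1 = 19%: (0.7840 + 0.3302)² / 0.01² = 12,413.

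| Reference rate | n, 5% relative | Power with 1,800 | n, 2.5% relative | Power with 1,800 |
|---|---|---|---|---|
| 5% | 58,793 | 7% | 236,899 | 4% |
| 10% | 27,873 | 10% | 112,264 | 5% |
| 20% | 12,413 | 18% | 49,947 | 7% |
| 30% | 7,260 | 28% | 29,174 | 10% |

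These are two-sided. One-sided, power for the 5% reduction at rates of 20% and 30% is 28% and 40%. The rate at which 1,800 gives exactly 80% is about 64% (5% reduction) or 88% (2.5%) two-sided, and 58% or 85% one-sided.

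**3. Planned totals.**
- All Table 3 sites: 1,000 + 5,000 + 1,000 + 30 + 175 + 1,000 + 200 + 300 + 4,500 + 100 + 300 + 1,600 = 15,205.
- Hospitalization, institutionalization and death (all sites except Twente): 15,205 − 300 = 14,905.
- Frailty incidence (Cork, Naples, Parma, Twente, Valencia): 5,000 + 175 + 1,000 + 300 + 1,600 = 8,075.
- S3: 200 to 400 as 20% implies a total of 1,000 to 2,000.

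**The case against.** The strongest defence is the absolute reading. The plan may have sized for the smaller effect and applied that number to every outcome. With 1,800 evaluable, a 2.5-point reduction then has at least 80% two-sided power at any rate up to about 18% (25% one-sided), and the 5-point outcomes have about 99%. This stands. A reader might infer that 2,000 is not an 80% size for any of the four reductions, or that the design simply lacks 80% power. The document supports neither, because it does not rule out absolute points at a suitable rate. The defence does not make 2,000 the size needed for hospitalization or institutionalization, and it fails for the 2.5-point outcomes at rates between about 18% and 83%.

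A reader might also take the precision origin as proven. It is a close match but an inference: the plan prints 5% as alpha and as a reduction, never as an expected proportion, and the absolute 2.5-point test at 18% fits as well.

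The notes attached to the 2,000 and to the Table 3 population column are not in the available text. The first might give a rate or scale. But no rate makes 2,000 the size for an absolute 5-point reduction, and only very high rates do so on the relative scale. The second might show that the column gives target populations rather than enrolment, which would remove the conflict with Table 3.

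Finally, Table 3 does not contradict every mention of 2,000. It is consistent with the Abstract's minimum and with 2,000 as a number needed. It conflicts only with the Sample section's approximate total and with the S3 counts.

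**Conclusion.** The point holds as wrong as written. The sample size, the named test and the 80% power do not fit together for all four outcomes on either scale at credible rates. On the absolute scale, two outcomes are greatly overpowered and the other two reach 80% only in part of the range of rates. On the relative scale, which is natural for an observed/expected ratio, 80% power needs rates near 64% and 88% two-sided (58% and 85% one-sided). Such rates are not credible for institutionalization or death in people living at home at entry and followed within a 36-month study. At assumed rates of 5% to 30%, two-sided power is about 7% to 28% for a 5% reduction and 4% to 10% for a 2.5% reduction.

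This rests on 1,800 evaluable people, the normal approximation and assumed reference rates. The mismatch with Table 3 is conditional on its column meaning participants.

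**What to change.** 1. For each outcome, state the reference rate from the named data flow, whether the reduction is absolute or relative, and whether the test is one- or two-sided.
2. Remove the interval width, confidence level and population size, or label them as a separate precision calculation.
3. Reconcile the planned totals across the Abstract, Sample, Sample size, Table 4 (S3) and Table 3, and say what the Table 3 column counts.
4. Restate power, or the smallest detectable reduction, at the number expected to be analysed: exposed participants and, for frailty incidence, those not frail at baseline. The Table 3 totals should not simply replace 2,000. Oporto and Salerno have control groups, which their counts may include, and the baseline assessment covers people who are already frail.
5. Where power is below 80%, say that the outcome will be estimated with a confidence interval, and drop the 80% claim for it.

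The cost is recalculation and text, with no added participants. The downside is that the stated power becomes less favourable for some outcomes.

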### Study sites

The proposal includes 12 implementation sites located in seven EU countries (Table 3). However the characteristic of the proposal is to be open to other contribution by other sites/stakeholders who will make themselves available to participate to the study

### Baseline assessment

The baseline assessment aims to stratify the population, (from robust to frail individuals) according to the risk on negative outcomes. The basis of the stratification is the operative definition of frailty above-mentioned.

The tool to be used should:

Identify frail individuals and size the risk of hospitalization, institutionalization and death as well as the trend of this risk during the follow up according to the exposure to interventions to cope with frailtyCover the five domains of frailty: social and economic resources, functional status, physical and mental health;Be short and easy to administer in order to involve thousands of citizens;Be simple in order to involve non –health professional personnel, such as the care-giver to administer it.

The working group reached a consensus on two common instruments for baseline assessment:

The **Risk Instrument for Screening in the Community** can be used to quickly screen large numbers of patients to identify and stratify those at greatest risk of three adverse healthcare outcomes (institutionalisation, hospitalisation and death) [10, 13, 37–41]. These patients can then be triaged for further assessment, investigation and treatment with integrated care bundles or other management strategies that are location or service specific. The RISC tool collects demographics, records concerns, the severity and ability of the caregiver network to manage three main domains (mental state, ADL state and medical state issues). It then summarises the perceived risk using a subjective, global score of risk based upon a five-point Likert scale measured from 1 (minimal-rare risk) to 5 (extreme-certain). The RISC was developed as an exemplar under the EIP on AHA reference site COLLAGE, Ireland’s only reference site for active and healthy ageing. It has been translated into multiple languages (English, Dutch, Italian, Spanish and Portuguese). It has been validated in multiple sites in the EU as part of work conducted in Action Group A3 of the EIP on AHA including in Porto (34) and Barcelona. The RISC stratifies risk of adverse healthcare outcomes by measuring the magnitude of functional, physical or state mental concern.

Sometimes although the concern may be minimal, the lack of formal and/or informal caregivers may elevate or even multiple that risk.

In order to better explore these borderline patients there is a need also to include a second instrument, aimed at assessing the risk of negative outcomes in individuals with no or minimal physical and/or cognitive impairment. **The Short Functional Geriatric Evaluation** is the synthesis of the Functional Geriatric Evaluation (FGE) questionnaire already validated for the predicting of negative outcomes within 5 years from the administration in an Italian population. The SFGE shows good correlation with the FGE [30,42] (Spearman Correlation = 0.82, p<0.001 tested on 203 individuals). This proposal will assess the harmonization of this procedure for the common baseline assessment with the different procedures developed by the projects embedded in the proposal in order to maximize the quantity and quality of information on the effectiveness of the implemented approaches.

### Follow up

According to the different program/projects intervention schemes, follow up data will be gathered every six-twelve months. The follow up will consist of the information that will be obtained following the baseline assessment on incidence of frailty, hospitalization, institutionalization and death. The study will run for 36 months in total including three months set up time and three months at the end to finalize the assessment (Fig 2)

Table 3 reports the list of study site with the list of data sources to be considered in the study for the comparisons. In some cases different kind of control groups will be also used: historical or ongoing cohort of citizens, assessed for frailty with comparable tools, who did not underwent any intervention will be involved in the data analysis. Data will be analyzed every six months

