**Genova**	Over 64 (about 30 Individuals)	Prospective observational Randomised trial (pilot)	-SFGE -RISC	In particular, DOREMI activities include: early risk detection of : ○ malnutrition ○ cognitive decline ○ social isolation ○ sedentariness ○ falls early risk ICT intervention based on social nudges and gamification to the promote active and healthy lifestyle and behavioral in respect to the four main risk factors : change and maintain healthy nutrition lifestyle reduce social isolation change and maintain an healthy physical lifestyle train cognitive function and reduce cognitive decline	Progression of frailty Incidence of hospitalization Incidence of institutionalization Incidence of death	a) Official sources (report on the hospitalization and mortality in Italy and UK released annually by EUROSTAT, ISTAT etc.); b) Passi d’Argento report (Regione Liguria) b) Other sources (data stems from the ongoing project).
Naples	Over 74 (175 ind.s)	Prospective observational	-SFGE -RISC	-Pro-active frailty screening/monitoring -Assistance in bureaucratic tasks -Referral to formal community-based or hospital-based services -Strengthening the social involvement of pre-frail older adults -Community-based health and ICT literacy activities including health promotion -Introduction of assessment of polypharmacy regimen	Incidence of frailty Progression of frailty Incidence of hospitalization Incidence of institutionalization Incidence of death	Official sources (report on the hospitalization and mortality in Campania region released annually by ISTAT and Ministry of Health); data stems from the ongoing Lazio Region Frailty Study carried out by the University of Tor Vergata, Regional pharmaceutical Data flows (evaluation of polypharmacy)

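### Expected events are not matched on calendar period, so sites that use annually released official rates cannot have same-year rates for the first impact report and probably not for the last follow-up year

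*Protocol article*

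**What the plan says.** - **Method.** Study design sets an observed/expected analysis (indirect standardisation). The reference population is matched on age, sex and place of residence; calendar period is not named. The comparison data are to be mainly those already available from established data flows. Table 4 (S2) likewise makes official sources the comparative data.
- **Timing.** Follow up states "follow up data will be gathered every six-twelve months" and "Data will be analyzed every six months". The study lasts 36 months, "including three months set up time and three months at the end to finalize the assessment".
- **First impact report.** Table 4 (S4) sets delivery at 31 December 2016, for citizens assessed before 30 June 2016. Development of the program also says end of 2016.
- **Reference sources (Table 3).** Parma lists only the "report on the hospitalization and mortality in Emilia Romagna region released annually by ISTAT and Ministry of Health". Naples lists the "report on the hospitalization and mortality in Campania region released annually by ISTAT and Ministry of Health", and the Rome row carries the same wording. Genova lists the "report on the hospitalization and mortality in Italy and UK released annually by EUROSTAT, ISTAT etc". Naples and Rome add an ongoing regional frailty study, and Genova adds other sources.
- **Other comparators.** Oporto, Salerno and Twente use control groups. Galway uses Cork as a sister study and also retrospective hospital data from one year before. Follow up allows, in some cases, a "historical or ongoing cohort of citizens, assessed for frailty with comparable tools".

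**The concern.** An observed/expected ratio has an expectation of 1 under no effect only if the reference rates apply to the time at which the events occurred. A report that is released once a year and covers a whole year cannot exist before that year ends. The protocol fixes a report date inside the year of follow-up and a close-out of three months, and it names annual reports as a source. At those sites, some events must therefore be compared with rates from an earlier year.

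If admission or death rates are falling in the population, the expected count is then too high and the programme appears to reduce events when it does nothing. If rates are rising, a true reduction is hidden. The error is a bias, so it does not shrink as sites are pooled, while the standard error does.

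**Working it through.** **1. First impact report (no assumption about delay).** The baseline group is classified from 1 April to 30 June 2016 (Table 4, S3), and the first six months are reported by 31 December 2016. The events fall in 2016. A full-year 2016 rate cannot exist by that date, so an annual official rate used there has a lag of at least one year.

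**2. Scope (Table 3 planned numbers).**
- Annual release stated: Genova 30 + Naples 175 + Parma 1,000 + Rome 4,500 = 5,705.
- All 12 sites: 1,000 + 5,000 + 1,000 + 30 + 175 + 1,000 + 200 + 300 + 4,500 + 100 + 300 + 1,600 = 15,205.
- Share: 5,705/15,205 = 37.5%. Parma, with no other source, is 1,000/15,205 = 6.6%.

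**3. Calendar of the final analysis.** Assume that the 36 months start on 15 January 2016, the earliest date in Table 4. The study then ends in mid-January 2019, and follow-up ends about mid-October 2018. A 2018 annual report would have to appear within about two weeks of the year's end. Person-time by calendar year:

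| Assumption on entry | 2016 | 2017 | 2018 |
|---|---|---|---|
| Follow-up months only (8.5, 12 and 9.5 of 30) | 28% | 40% | 32% |
| Uniform entry April 2016 to March 2017, followed to 15 October 2018 | 13.9% | 47.5% | 38.6% |

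So 32-39% lies in 2018. Under the second pattern, 13.9% + 47.5% = 61% could have same-year rates if 2017 rates are out.

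**4. Size of the shift.** With no programme effect, a yearly relative fall t and a lag of L years, the ratio is (1 - t)^L. The documents give no trend, so t = 1-3% is assumed.
- L = 1: apparent reduction 1.0%, 2.0% and 3.0% for t = 1%, 2% and 3%.
- L = 2: 2.0%, 4.0% and 5.9%.

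For the final analysis, shift ≈ t × Σ(share × lag), with the uniform-entry shares:

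| Latest published year (assumed) | Mean lag, years | Shift for t = 1-3% |
|---|---|---|
| 2017 | 0.386 × 1 = 0.39 | 0.4-1.2% |
| 2016 | 0.475 × 1 + 0.386 × 2 = 1.25 | 1.2-3.7% |
| 2015 | 0.139 × 1 + 0.475 × 2 + 0.386 × 3 = 2.25 | 2.2-6.7% |

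With the month-based shares, the mean lags are 0.32, 1.03 and 2.03 years.

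**5. Effect on the test (illustration).** Assume an expected risk of 20%, t = 2% and a one-year lag for everyone, so that the true risk is 19.6%. The chance of a falsely favourable result is Φ{[0.004 - 1.96√(0.2 × 0.8/n)] / √(0.196 × 0.804/n)}, against a nominal 2.5% in that direction. It is 6.1% at n = 1,800 (2,000 less 10% loss) and 11% at n = 5,705.

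**6. Against the planned effects.** Sample size gives reductions of 2.5% (frailty incidence, death) and 5% (hospitalization, institutionalization) without saying whether they are relative or absolute. If relative, the shifts above are of similar size. If absolute, take the baseline of about 18% at which a two-sided one-proportion test for 2.5 points needs 1,800 subjects: a 1-3% relative shift is then 0.18-0.54 points, well below 2.5. The stated 2,000 cannot be reproduced, because the text shown gives no expected rate. The point does not depend on it.

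**The case against.** A reader might infer that every analysis, the final one included, must use earlier-year rates, and that any yearly trend will therefore appear as a programme effect across the whole study. The documents do not support that.

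- Annual release is stated for 4 of 12 sites and for hospitalization and mortality only. Three of the four list further sources, and national, regional or local data flows of unstated frequency are allowed. Three sites use control groups, where publication lag does not arise, and cohorts may be ongoing and not only historical.
- At the final analysis, 2016 and 2017 person-time can be year-matched if those rates are out. No publication delay is stated.
- A rising trend hides an effect; it does not create one.
- The one certain lag falls on a small report. Table 4 (S3) gives about 200-400 citizens. At an assumed 20% yearly risk, 400 people followed for six months yield about 40 events and a relative standard error near 1/√40 = 16%, far above a 1-3% shift.
- Choice of reference year is ordinary analysis-plan content, and the analysis plan is not shown.

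All but the last limit the scope or size of the point, and they stand. The last stands only in part. An analysis plan can choose a reference year, but it cannot make 2016 annual rates exist by 31 December 2016. The report date, the source and the matching variables are all fixed in the protocol.

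**Conclusion.** The point holds in a limited form. Calendar period is not among the matching variables. At the four sites with annually released official rates, any such rate in the December 2016 report dates from 2015 or earlier; this follows from the stated dates. For the final analysis, same-year official rates are very unlikely for the last follow-up year, which rests on the assumed January 2016 start. Galway's prior-year data and any historical cohorts carry a similar gap.

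The size depends on a trend of 1-3% a year and on publication delays that the documents do not give: a shift of 1-3% at a one-year lag, about 0.4-1.2% at the final analysis if 2017 rates are out, and more if only older rates are. The claim that the drift matches the planned reductions should not be made without the condition that those reductions are relative.

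**What to change.** 1. Compute expected counts in age × sex × calendar-year cells within location, using rates for the same calendar year.
2. At each analysis, end the official-rate observed/expected window on 31 December of the latest year with published rates, and report later events without a ratio. Where a local data flow gives current counts, use those instead.
3. Label the official-rate comparison in the 31 December 2016 report provisional or descriptive, and re-run it when 2016 rates appear.
4. Adjust historical cohorts and prior-year data for calendar period, or keep them descriptive.
5. State the reference year beside each ratio.

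The cost is wording in the protocol or analysis plan; no new data need be collected from participants. The downside is that interim ratios lose the most recent person-time, and the final official-rate ratio either stops at the end of 2017 or waits for the 2018 rates.
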